#### Outcomes Assessment

A blinded multidisciplinary team composed of a nephrologist, cardiologist, and nurse will follow participants and review medical records and adjudicate outcomes and end points in the study.

A medical appointment will be scheduled for weeks 0, 13, 26, 39, and 52, where the multidisciplinary team will assess the primary and secondary outcomes and report them to the Data Coordinating Center (DCC). At each visit, a venous blood sample (5 mL) will be collected in order to measure hematocrit, hemoglobin, and platelet hyperreactivity.

After the end of the treatment phase of the trial, participants will be followed for an additional 6 months to assess further adverse events. For that purpose, the multidisciplinary team will contact patients monthly during their hemodialysis sessions. The total length of the study will be 30 months.

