#### Participant Timeline

The schedule and procedures during patient visits to the participating center (recruitment, hemodialysis sessions, and monthly assessment of outcomes) are summarized in Table 1.

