#### Recruitment

The estimated hemodialysis admission rate at a large dialysis center is 50 patients per month. Therefore, we expect to include 8 to 10 patients every week, completing our recruitment goal in 9 months. We propose a recruitment period of 12 months in case enrollment is slower than expected.

Eligible patients will be identified using medical records, clinician invitation letters, and internal flyers posted in patient areas. The study team will approach eligible patients to invite them to participate in the trial. All aspects of the study will be explained and all participants who agree to participate must provide written informed consent. One venous blood sample will be collected prior to randomization in order to assess platelet reactivity profile, a stratification factor for randomization.

**Table 1 table1:** Schedule and procedures during patient visits to the participating center.

Procedure	Enrollment phase (12 months)	Experimental phase (12 months)					Follow-up (6 months)
	Preliminary visit (369 to 3 days before the experimental phase)	First medical visit (day 0)	Hemodialysis sessions (approximately every 3 days)	Every 30 days	Weeks 13, 26, 39 and 52	Hemodialysis sessions (every 30 days)	
Informed consent form	X^a^						
Physical exam/medical history and medication review	X						
Inclusion/Exclusion	X						
Collection of a blood sample^b^		X			X		
Randomization		X					
Patients’ meeting with the study team and oral training about compliance to treatment		X		X			
Provision of the necessary number of pills (on a monthly basis)		X		X			
Patients’ training focused on compliance (short educative video)			X				
Counting of returned pills				X			
Blinding assessment (questionnaire)				X			
Measurement of primary and secondary outcomes^c^ during consultations with a nephrologist and a cardiologist		X			X		
Assessment of later bleeding adverse events						X	

^a^X indicates the time at which each procedure will occur.

^b^Assessment of the hematocrit, hemoglobin concentration, and platelet hyperreactivity profile.

^c^Number of events for cardiac death, nonfatal myocardial infarction, nonfatal stroke, arteriovenous fistula thrombosis, and assessment of major and minor bleeding using the Thrombolysis in Myocardial Infarction scale.

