### Data Collection, Management Analysis, and Monitoring

#### Data Collection

We intend to minimize missing data by having monthly visits with patients. An adherence check will be done by counting returned tablets as previously stated.

Regarding data collection and storage, the study team will be trained to oversee all key aspects of the protocol: (1) methodology, forms, and tools that must be used for the collection, entry, monitoring, and editing of data; (2) appropriated methods to communicate among investigators and between investigators and participants; and (3) importance of reporting data as close to real time as possible during the course of the study.

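### Participant Timeline promises monthly outcome assessment, but Outcomes Assessment and Table 1 schedule it every 13 weeks on study drug, so scheduled bleeding checks are sparser during treatment than after it

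*Protocol article*

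**What the plan says.** Three places in the Protocol article describe how often outcomes are assessed during the 12 months of treatment.

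- **Participant Timeline** introduces the visit schedule with the words "recruitment, hemodialysis sessions, and monthly assessment of outcomes) are summarized in Table 1".
- **Outcomes Assessment** gives a quarterly schedule: "A medical appointment will be scheduled for weeks 0, 13, 26, 39, and 52". The multidisciplinary team assesses the primary and secondary outcomes at these appointments and reports them to the Data Coordinating Center. Blood for hemoglobin, hematocrit and platelet reactivity is drawn at the same visits.
- **Table 1** has a row headed "Measurement of primary and secondary outcomes^c^ during consultations with a nephrologist and a cardiologist". It is marked at day 0 and at weeks 13, 26, 39 and 52, and not in the 30-day column. The 30-day column covers the study-team meeting with compliance training, pill supply, the count of returned pills and the blinding questionnaire. The Adherence section describes these monthly visits in the same way, as visits to check adherence and answer questions.

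For the 6 months after treatment, Outcomes Assessment says that "participants will be followed for an additional 6 months to assess further adverse events", and that for this purpose "the multidisciplinary team will contact patients monthly during their hemodialysis sessions". The matching row of Table 1 reads "Assessment of later bleeding adverse events" and is marked every 30 days. No thrombotic outcome is scheduled in that phase.

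Data Collection relies on the monthly visits to minimize missing data and lists among its training topics the "importance of reporting data as close to real time as possible during the course of the study".

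**The concern.** The article prints an explicit schedule and then describes it wrongly. A site cannot tell whether events are to be asked about each month or each quarter during treatment.

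If the quarterly schedule is the intended one, bleeding is looked for on a regular timetable less often while patients take the study drug than after they stop. The article gives no reason for this, although its Background names aspirin's safety in this population as a gap in knowledge and cites an apparent increase in minor bleeding.

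The outcome most exposed is TIMI minor bleeding. It requires overt bleeding with a hemoglobin drop of 3 to 5 g/dL, while study hemoglobin is drawn only every 13 weeks. A bleed that did not lead to hospital care may be forgotten, or the hemoglobin may recover, before the next appointment. It may also go unrecorded if the patient withdraws, transfers or dies first. Under Statistical Methods, a missed event changes the proportion compared by the chi-square test. An imprecise date affects the time-to-event analyses.

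**Working it through.** The plan states no figure for assessment lag, so there is none to reproduce. The check compares the schedules and then works out what the intervals imply.

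**Step 1: schedules side by side.**

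| Source | On treatment (12 months) | After treatment (6 months) |
|---|---|---|
| Participant Timeline | Outcomes monthly | Not separately stated |
| Outcomes Assessment | Outcomes at weeks 0, 13, 26, 39, 52 | Adverse events, monthly contact |
| Table 1 | Outcomes at day 0 and weeks 13, 26, 39, 52; none in the 30-day column | Bleeding every 30 days |

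Outcomes Assessment and Table 1 agree with each other. Participant Timeline agrees with neither for the treatment phase. The comparison of on-drug with off-drug frequency can be made for bleeding only, because no thrombotic check is scheduled after treatment.

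**Step 2: intervals and counts.**

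- On drug: 13 weeks x 7 = 91 days between checks; 4 post-baseline checks in 12 months.
- Off drug: 30 days between checks; about 6 checks in 6 months.
- Ratio of intervals: 91/30 = 3.0.

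**Step 3: wait from event to next scheduled check.** Two assumptions are made: events fall evenly between checks, and scheduled checks are the only way an event is found. The mean wait is then half the interval.

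- On drug: 91/2 = 45.5 days, maximum 91.
- Off drug: 30/2 = 15 days, maximum 30.
- Share of on-drug events waiting more than 30 days: (91 - 30)/91 = 67%.

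The second assumption is not what the article describes. It also provides for review of medical records, so these waits are upper bounds.

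**Step 4: number of major bleeds.** Sample Size assumes 1-year TIMI major bleeding of 2.5% on aspirin and 1% on placebo, with 171 patients per arm.

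- Aspirin: 171 x 0.025 = 4.3.
- Placebo: 171 x 0.01 = 1.7.
- Total: about 6.0.

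This shows how few major bleeds are expected. It does not estimate how many would be missed. The article gives no rate for minor bleeding, the outcome most at risk, so under-capture there cannot be sized from the document.

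**The case against.** The strongest reply is that the quarterly appointments are not the only route by which events become known.

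- Outcomes Assessment first says that a blinded team follows participants, reviews medical records and adjudicates outcomes, and it sets no quarterly limit on this.
- Emergency Unblinding has investigators discuss unblinding with a monitoring board advisor within 24 hours when severe adverse events occur. This presupposes that such events are known between visits.
- Patients dialyze about every 3 days at the single trial center. A fistula thrombosis affects the access used for dialysis. A TIMI major bleed is intracranial, fatal, or overt with a hemoglobin drop of at least 5 g/dL or a 15% absolute fall in hematocrit. Neither is likely to wait for a quarterly question.

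This largely stands. It does not fully cover minor bleeding: the 24-hour route concerns severe events, and record review finds only what was recorded.

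A second reply is that both arms share one schedule under blinding, so the aspirin-placebo comparison is not shown to be biased. That also stands.

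A third is that the content of the monthly forms may be in the full protocol, which is not shown, and that near-real-time reporting is only a training topic. That is fair, and the lack of a form is not counted here as an omission. It does not explain why the article's own description of Table 1 differs from Table 1.

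A reader might infer more: that thrombotic outcomes too are checked monthly after treatment, that on-treatment major bleeds will reach the monitoring board late or be missed, or that a comparison of on-drug with off-drug bleeding will be distorted. The document does not support these readings. Only bleeding is marked after treatment, late detection of major bleeds is conjecture given the other routes, and Statistical Methods plans no on-drug versus off-drug comparison.

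**Conclusion.** The point holds as a contradiction in the stated schedule, with a moderate consequence for event capture. Monthly outcome assessment, as Participant Timeline describes it, appears in neither Outcomes Assessment nor Table 1. As written, scheduled bleeding checks are 91 days apart on study drug and about 30 days apart off it, and the 30-day visits on treatment list no bleeding or event check.

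The likely consequence is under-capture or imprecise dating of non-hospitalized events, chiefly TIMI minor bleeding. Most major bleeds and fistula thromboses should be found by other means. The mean waits of 45.5 and 15 days are upper bounds resting on the two assumptions given with them. No bias between the arms is shown. The change is worth making because it removes a stated contradiction and improves capture at visits that already take place.

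**What to change.** Reconcile Participant Timeline, Outcomes Assessment and Table 1 so that they give one frequency of outcome assessment during treatment.

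Add a short bleeding and thrombotic-event form, with the date of each event, to the study-team visit already held every 30 days on treatment, and send it to the Data Coordinating Center at that visit. Mark event capture in the 30-day column of Table 1. Keep the quarterly appointments for full assessment and adjudication.

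The cost is a few extra questions at existing visits and one more form in the database. No new visits are needed.

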#### Study Variables

The outcome variables are the incidence of cardiac death, nonfatal myocardial infarction, nonfatal stroke, and arteriovenous fistula thrombosis, as well as the presence or absence of bleeding and its severity based on TIMI criteria [19]. The treatment variables are the exposure to the intervention (aspirin 100 mg/d or placebo). The stratification variables are the presence versus absence of type 2 diabetes mellitus and the presence versus absence of platelet hyperreactivity.

#### Participant Timeline

The schedule and procedures during patient visits to the participating center (recruitment, hemodialysis sessions, and monthly assessment of outcomes) are summarized in Table 1.

#### Sample Size

Sample size was calculated based on estimates for the rate of events in the primary composite outcome over 1 year: TIMI major bleeding (placebo 1% vs aspirin 2.5% [15]), cardiovascular events (placebo 3.0% vs aspirin 2.5% [10]), and fistula thrombosis (placebo 19% vs aspirin 8% [23]), for a total 1-year event rate of 23% in the placebo group and 13% in the aspirin group. A sample size of 318 patients (159 per arm) provides 80% power to detect a difference between groups of this magnitude (corresponding to an HR of 0.53) using a 2-sided log-rank test and alpha=.05 (Power Analysis and Sample Size Software version 14, NCSS LLC). The sample size for the trial was increased to 342 patients (171 per arm) to account for estimated attrition of 10%.

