## Methods

### Participants, Interventions, and Outcomes

#### Study Design

We will perform a phase 2 randomized, single-center, placebo-controlled, triple-blind, superiority clinical trial with 1:1 allocation to receive either 100 mg of aspirin per day or placebo by mouth for 12 months. Randomization will be stratified based on 2 baseline characteristics: (1) the presence versus absence of type 2 diabetes mellitus and (2) the presence versus absence of platelet hyperreactivity. The study will start following approval of the Institutional Review Board (IRB) and will follow the ethical principles of the Declaration of Helsinki of the World Medical Association. The study design is illustrated in Figure 1.

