#### Outcomes

The primary outcome is the incidence of a composite event including all of the following: cardiac death, nonfatal myocardial infarction, nonfatal stroke, arteriovenous fistula thrombosis, and TIMI major bleeding [19] by 12 months of treatment. The secondary outcomes are effect modification of treatment efficacy by the presence of type 2 diabetes mellitus or platelet hyperreactivity and the rate of TIMI minor bleeding between treatment groups.

According to the TIMI criteria, major bleeding is defined as the presence of any intracranial bleeding (excluding microhemorrhages <10 mm evident only on gradient-echo magnetic resonance imaging), fatal bleeding (bleeding that directly results in death within 7 days), or clinically overt signs of hemorrhage associated with a drop in hemoglobin of ≥5 g/dL or a ≥15% absolute decrease in hematocrit [19]. Minor bleeding is defined as clinically overt with a hemoglobin drop of 3 to 5 g/dL [19].

The profile of platelet reactivity will be determined by multiple electrode aggregometry using a Multiplate analyzer (Dynabyte GmBH). This method was chosen because it currently is the most efficient assay used to assess platelet reactivity in humans [21]. The Multiplate will measure platelet activity (defined as aggregation capability after activation with adenosine diphosphate) as the area under the curve reported in area units multiplied by time (AU×min). Platelet hyperreactivity is defined based on the manufacturer’s recommendations and published data, with a cutoff of 50 AU×min for adenosine diphosphate–induced aggregation [22].

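### With the 12-month primary endpoint, 318 patients give about 65% power for 23% vs 13%, not the stated 80%; the figure reproduces only with follow-up beyond 12 months

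*Protocol article*

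**What the plan says.** The Sample Size section adds up component rates "for a total 1-year event rate of 23% in the placebo group and 13% in the aspirin group", "corresponding to an HR of 0.53". It then states "A sample size of 318 patients (159 per arm) provides 80% power to detect a difference between groups of this magnitude", "using a 2-sided log-rank test and alpha=.05". Enrolment is raised to 342 for attrition. The section gives no accrual or follow-up time for the calculation.

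The rest of the protocol fixes the window. Study Design describes a trial "with 1:1 allocation to receive either 100 mg of aspirin per day or placebo by mouth for 12 months". Outcomes defines the primary composite, ending with "TIMI major bleeding [19] by 12 months of treatment". The objective in the Abstract is also a comparison of 12-month rates. Statistical Methods analyses time to first event by Kaplan-Meier curves and a log-rank test. The scheduled outcome visits end at week 52. The six months after treatment are for further adverse events (Outcomes Assessment), and the matching row of Table 1 reads "Assessment of later bleeding adverse events".

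**The concern.** The power of a log-rank test depends on the number of events. A mean 12-month incidence of 18% in 318 patients gives fewer than 60 events, which looks too few for 80% power at a hazard ratio near 0.53. If so, the trial would start with a materially higher type II error than its ethics committee and readers are told. A non-significant result would also be weaker evidence against benefit than the stated power implies.

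**Working it through.** **Inputs, all from the protocol.** 1-year rates of 23% and 13%, HR 0.53, two-sided alpha .05, log-rank test, 318 patients in 1:1 allocation (Sample Size, Study Design); events counted to 12 months (Outcomes); recruitment over 12 months (Recruitment). Event times are taken as exponential, so that the 1-year rates fix the hazards.

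**1. Hazard ratio.** −ln(0.87) / −ln(0.77) = 0.1393 / 0.2614 = 0.533. The stated 0.53 reproduces.

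**2. Events needed for 80% power.**
- Schoenfeld: 4 × (1.96 + 0.8416)² / (ln 0.533)² = 79.2.
- Freedman: (1.96 + 0.8416)² × [(1 + 0.533) / (1 − 0.533)]² = 84.5.

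**3. Events available with 12 months per patient.** Mean incidence is (0.23 + 0.13) / 2 = 0.18, so 318 × 0.18 = 57.2 events.

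**4. Power at 318.**
- Schoenfeld: Φ(√57.2 / 2 × 0.629 − 1.96) = Φ(0.42) = 66%.
- Freedman: Φ(√57.2 × 0.467 / 1.533 − 1.96) = Φ(0.35) = 64%.
- Two proportions, 159 per arm: 64% to 65%, depending on the variance formula.
- Simulated log-rank trials (two runs of 15,000 and 20,000): 64% to 65%.

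**5. Patients needed for 80% at 12 months.** 79.2 / 0.18 = 440 (Schoenfeld) and 84.5 / 0.18 = 469 (Freedman). Comparing two proportions gives 462. These are evaluable patients, before attrition.

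**6. Does the attrition allowance help?** With 342 enrolled and 10% loss spread over the year, simulated power is 65%.

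**7. Which follow-up reproduces 318?**

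| Follow-up per patient | Event probability (placebo / aspirin) | Events at 318 | N for 80% (Schoenfeld to Freedman) |
|---|---|---|---|
| 12 months (the design) | 23% / 13% | 57 | 440 to 469 |
| 12 to 24 months (12-month uniform accrual, common close at month 24) | 32.2% / 18.8% | 81 | 310 to 331 |
| Fixed 18 months | 32.4% / 18.9% | 82 | 309 to 330 |

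The stated 318 lies inside the second and third ranges; simulated power under the common close is 79% to 80%. Using HR 0.53 in place of 0.533, a continuity correction, a one-sided alpha or the rates read as hazards does not give 318 at 80% with 12 months of follow-up. One-sided power, which the protocol does not use, would be 77%.

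**8. Difference detectable at 80% with 318 and 12 months.** With placebo at 23%, the aspirin rate would have to be about 11.1% (Freedman) to 11.5% (Schoenfeld), a hazard ratio of about 0.45 to 0.47.

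**The case against.** The arithmetic at 12 months is not open to serious dispute; the counter-arguments concern what is built on it.

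- **The cause is inferred.** The article does not report the accrual and follow-up entered into the software, and an article may leave such inputs out. A fixed 18 months reproduces 318 as well as a common close at month 24 does. This stands: the common close is a likely explanation, not an established one. Every pattern found that returns 318 still needs follow-up beyond 12 months.
- **Later thrombotic events might be recorded.** Outcomes Assessment speaks of adverse events in general during the extra six months, which is broader than the bleeding row in Table 1. This also stands, so Table 1 is supporting evidence only. What excludes later events from the primary analysis is the outcome definition, which stops at 12 months of treatment.
- **Restating the power leaves the trial small.** The trial has no approval, registration or dates yet, so a larger sample or a longer counting window is still open. That is a fair point about design, but it is a costlier choice for the sponsor. It is no reason to leave a wrong figure in place.

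**Conclusion.** The concern holds. For the endpoint as defined, 318 patients give about 57 first events and 64% to 66% power for 23% vs 13%, roughly 15 points below the stated 80%. The type II error for the planned effect is about 35%, not 20%. This rests on the protocol's own rates, alpha and test, exponential event times and full 12-month follow-up; the two-proportions check does not need the exponential assumption and agrees. The explanation that patients were credited with up to 24 months of follow-up is likely but unconfirmed, and the shortfall does not depend on it.

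**What to change.** Rewrite the Sample Size paragraph for 12-month follow-up and state the follow-up used. It should say that 318 evaluable patients are expected to give about 57 first events, with about 65% power for 23% vs 13% (HR 0.53). It should add that 80% power is reached only for about 23% vs 11.1% to 11.5% (HR about 0.45 to 0.47, depending on the formula). The claim of 80% for the planned difference should be removed. The cost is one paragraph and a less favourable power figure, with no extra patients.

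If the sponsor wants 80% for 23% vs 13%, that is a separate and costlier decision. It would take about 440 to 470 evaluable patients before attrition, or a primary endpoint counted over a longer period. For the latter, the outcome, treatment and visit passages would have to be reconciled with one another.

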#### Recruitment

The estimated hemodialysis admission rate at a large dialysis center is 50 patients per month. Therefore, we expect to include 8 to 10 patients every week, completing our recruitment goal in 9 months. We propose a recruitment period of 12 months in case enrollment is slower than expected.

Eligible patients will be identified using medical records, clinician invitation letters, and internal flyers posted in patient areas. The study team will approach eligible patients to invite them to participate in the trial. All aspects of the study will be explained and all participants who agree to participate must provide written informed consent. One venous blood sample will be collected prior to randomization in order to assess platelet reactivity profile, a stratification factor for randomization.

**Table 1 table1:** Schedule and procedures during patient visits to the participating center.

Procedure	Enrollment phase (12 months)	Experimental phase (12 months)					Follow-up (6 months)
	Preliminary visit (369 to 3 days before the experimental phase)	First medical visit (day 0)	Hemodialysis sessions (approximately every 3 days)	Every 30 days	Weeks 13, 26, 39 and 52	Hemodialysis sessions (every 30 days)	
Informed consent form	X^a^						
Physical exam/medical history and medication review	X						
Inclusion/Exclusion	X						
Collection of a blood sample^b^		X			X		
Randomization		X					
Patients’ meeting with the study team and oral training about compliance to treatment		X		X			
Provision of the necessary number of pills (on a monthly basis)		X		X			
Patients’ training focused on compliance (short educative video)			X				
Counting of returned pills				X			
Blinding assessment (questionnaire)				X			
Measurement of primary and secondary outcomes^c^ during consultations with a nephrologist and a cardiologist		X			X		
Assessment of later bleeding adverse events						X	

^a^X indicates the time at which each procedure will occur.

^b^Assessment of the hematocrit, hemoglobin concentration, and platelet hyperreactivity profile.

^c^Number of events for cardiac death, nonfatal myocardial infarction, nonfatal stroke, arteriovenous fistula thrombosis, and assessment of major and minor bleeding using the Thrombolysis in Myocardial Infarction scale.

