#### Eligibility Criteria

The study population consists of men or women with ESRD who are at least 18 years of age and have started chronic intermittent hemodialysis in the previous 3 months.

Exclusion criteria include any contraindications to ASA, concurrent treatment with anticoagulants or platelet aggregation inhibitors, and pregnancy or lactation. Patients with life-threatening conditions other than renal or vascular disease will also be excluded from the trial: all types of cancer, liver disease, AIDS, or severe lung disease. ESRD due to glomerulopathy has a different pattern of mortality [20], which precludes its inclusion in this trial. Patients on other modalities of RRT will also be excluded.

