#### Interventions

The intervention is an enteric-coated oral pill containing 100 mg of ASA, administered once daily, after lunch, over 12 months. The comparator will be a placebo tablet with the same characteristics as the active pills. Both arms will have the same administration schedule and will start treatment the day after randomization (day 0).

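### Table 1 allows the only eligibility and medication check up to 369 days before day 0, which does not fit a population newly started on hemodialysis

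*Protocol article*

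**What the plan says.** Eligibility Criteria limits the trial to adults with ESRD who "have started chronic intermittent hemodialysis in the previous 3 months". It gives no date from which those months are counted. The same section excludes patients with any contraindication to aspirin, and also "concurrent treatment with anticoagulants or platelet aggregation inhibitors, and pregnancy or lactation". Cancer, liver disease, AIDS and severe lung disease are further exclusions.

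Table 1, in the Recruitment section, sets out when each procedure takes place. Its first column, under a heading for a 12-month enrollment phase, is labelled "Preliminary visit (369 to 3 days before the experimental phase". Three rows have their only mark there: informed consent, "Physical exam/medical history and medication review", and the inclusion/exclusion check.

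The next column, "First medical visit (day 0", marks the blood sample, randomization, the study-team meeting, the supply of pills and the outcome measurement. It marks neither eligibility nor medication review. Interventions says that both arms "will start treatment the day after randomization (day 0". Nothing else in the article describes an eligibility check between the preliminary visit and randomization.

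**The concern.** Eligibility should describe the patients who are randomized, at about the time they are randomized. Here the printed schedule lets the two drift apart by up to a year.

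Two things are at stake. First, the trial is meant for people new to hemodialysis. A year's gap would admit people who are no longer new to it. Second, several exclusions can change within a year: contraindications to aspirin, use of anticoagulants or other antiplatelet agents, and pregnancy. On the printed schedule, study drug could start without the protocol's own exclusions having been checked again.

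Statistical Methods specifies an intention-to-treat analysis of all randomized patients. Anyone randomized after becoming ineligible would therefore stay in the primary analysis, so the problem has to be prevented at entry.

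**Working it through.** This is date arithmetic; no power or sample-size figure is involved.

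**Inputs**
- Screening window: 369 to 3 days before the experimental phase (Table 1).
- Time on hemodialysis: started in the previous 3 months (Eligibility Criteria), taken as 91.3 days at 30.4375 days per month.
- Start of the experimental phase: day 0, where Table 1 places randomization.
- Recruitment period: 12 months (Recruitment: "We propose a recruitment period of 12 months in case enrollment is slower than expected").
- Total study length: 30 months (Outcomes Assessment).

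**Step 1: where the 369 days probably come from.** Width of the window = 369 − 3 = 366 days; 366 / 30.4375 = 12.0 months. This equals the enrollment phase printed above the column. The likely origin is the trial's recruitment calendar with a 3-day minimum gap.

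**Step 2: longest time on hemodialysis at day 0, counting the 3 months to screening.** Maximum = screening gap + 91.3 days.

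| Screening gap (days) | Maximum at day 0 (days) | Months |
|---|---|---|
| 3 | 94.3 | 3.1 |
| 30 | 121.3 | 4.0 |
| 90 | 181.3 | 6.0 |
| 369 | 460.3 | 15.1 |

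The longest permitted gap alone is 369 / 91.3 = 4.0 times the 3-month limit. The maximum at day 0 is 460.3 / 91.3 = 5.0 times that limit.

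**Step 3: counting the 3 months to randomization instead.** Any gap longer than about 91 days then breaks the criterion, even for a patient who began hemodialysis on the day of screening. The part of the window this covers is (369 − 91) / (369 − 3) = 278 / 366 = 76%. This is a share of permitted days. It does not estimate the share of patients affected, which the article gives no means of calculating.

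**Step 4: age of the exclusion check.** The oldest permitted check is 369 / 30.4375 = 12.1 months before day 0. This holds whichever date anchors the 3 months. If day 0 is read as the day after randomization, the figures shift by one day, which does not matter.

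**Step 5: does the total length settle the reading?** It does not. With rolling entry, the last patient enters at month 12 and adds 12 months of treatment and 6 of follow-up, giving 30. If everyone started after enrollment closed, the sum is again 12 + 12 + 6 = 30.

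**The case against.** The strongest reply is that nobody intends a year's wait. Recruitment expects 8 to 10 patients to be included every week, which reads as continuous entry. No sentence holds randomization until enrollment closes or says that a screening result stays valid for a year. This is persuasive about intent, and it makes the 15-month figure a worst case rather than an expected value. It does not correct the table. The column gives an interval before the experimental phase, and Participant Timeline presents the table as the schedule of patient visits.

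A second reply is that the 3-month criterion may be counted to consent or screening. This stands. A reader might infer that Table 1 flatly contradicts the criterion, but with no anchor date given, that is true only on one reading.

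A third is that day 0 is not free of checks. This also stands. A blood sample is taken, and outcomes, including fistula thrombosis and bleeding, are assessed in consultations with a nephrologist and a cardiologist. What is missing is the eligibility check and the medication review. A fistula that thrombosed during the wait would not be an example of an outdated exclusion, because fistula thrombosis is not an exclusion criterion.

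Finally, a condensed article may leave re-confirmation of eligibility to the full protocol. That would answer a complaint about silence. Here the article prints a specific window and a specific placement of the checks, and these do not fit its own population.

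**Conclusion.** The point holds as a scheduling error that needs correction. As printed, a patient could be randomized up to about 15 months after starting hemodialysis, with changeable exclusions last checked up to a year before. The 15-month figure assumes that the column is a per-patient window and that the 3 months are counted to screening. If they are counted to randomization, the window and the criterion contradict each other directly. The age of the exclusion check depends only on the per-patient reading.

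A reader might go further and infer that patients must survive to day 0, so that early high-risk time is lost and the event rate falls. The article does not support this. It gives no event rates by time on hemodialysis, and Sample Size uses single 1-year rates. Nor does it show that any patient is actually planned to wait a year.

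**What to change.** 1. In Table 1, replace the 369-to-3-day label with a true per-patient screening window that is consistent with the 3-month criterion. Keep the 12-month enrollment phase as a separate, trial-level item.
2. Mark the inclusion/exclusion check and the medication review at day 0 as well, before randomization.
3. In Eligibility Criteria, state the date from which the 3 months are counted, and reconcile that section with Table 1. Which date to use is for the investigators to decide.

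The cost is one column label, two added marks and one sentence. Day 0 is already a medical visit, so no visit is added. A few screened patients may prove ineligible at day 0 and would need to be replaced before randomization.
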